### Methods for additional analyses (e.g. subgroup analyses) {20b}

Subgroup analyses will be conducted by psychiatric diagnosis (psychosis vs. no psychosis). The latter is important since psychosis is a key risk factor for aggression.

### Methods in analysis to handle protocol non-adherence and any statistical methods to handle missing data {20c}

Data will be analysed on an intention-to-treat basis such that the last observations will be carried forward. Otherwise, depending on the pattern of missing data in the last observation, e.g. if missing at random, multiple imputations technique will be used to deal with missing data [32].

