### Criteria for discontinuing or modifying allocated interventions {11b}

Discontinuation rules for individual participants include withdrawal of consent, development of a coincidental health problem/illness, or exacerbation of aggressive behaviours expressed as a report of a serious violent incident and/or an increased incidence of self-harm or self-injurious behaviour as judged by their caregivers. Additionally, the study could stop early if the intervention significantly exacerbates aggressive, impulsive, or self-harming behaviours as judged by the trial investigators.

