### Outcomes {12}

#### Primary outcome measure

##### Aggression

The *Modified Overt Aggression Scale* (MOAS) [20] will be used as a repeated measure to assess aggressive behaviours at baseline, 1 week (day 10), and 1 month (day 38) following the last tDCS treatment. MOAS is an informant-rated scale which will be completed by a member of care staff who have professional knowledge of the participant. MOAS has four domains (Verbal Aggression, Aggression Against Property, Autoaggression, and Physical Aggression) which are weighted and each rated on a 5-point scale (0–4). Scoring of MOAS yields weighted scores, total and by domain. MOAS is considered to be a reliable measure of aggressive behaviours in people with IDD [21].

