**Fig. 1 Fig1:**
[figure not shown]
Trial CONSORT diagram. Stop signal task (SST), Behavior Problems Inventory (BPI), Barratt Impulsiveness Scale version 11 (BIS-11), Modified Overt Aggression Scale (MOAS)

Participant healthcare records will be examined to obtain information concerning the diagnosis of IDD, demographics, number and duration of admissions to psychiatric institutions, and current psychotropic medication regime. A member of staff at the participant’s residence with good professional knowledge of the participant will be asked to complete the BPI and MOAS at baseline and 1 week after the last tDCS stimulation. At baseline, participants will be asked to complete the modified BIS-11, and SST. Three tDCS sessions will be delivered over three successive days (one session daily). Participants will be asked to repeat SST at the end of the third session (Fig. 1). Additionally, a tDCS adverse effects questionnaire will be administered following each tDCS treatment to detect adverse effects. At 1 week and also 1 month following the third and final treatment, participants will complete the BPI and MOAS and will be debriefed to unblind them to treatment arm.

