## Statistical methods

### Statistical methods for primary and secondary outcomes {20a}

Behavioural outcome measures will be analysed using the Statistical Package for Social Sciences (SPSS; Version 26). A 2 × 2 Repeated Measures ANOVA will be performed with group allocation (active tDCS vs. sham tDCS) and time (pre- vs. post-tDCS stimulation). Post tDCS measures for MOAS, SST, and BPI-S will be treated separately as repeated measures. Total scores on BIS-11 will be entered into the analysis as a covariate. Significant main effects and interactions will be explored using simple effects analysis. For instance, within-subject factors will be used to compare changes in outcome variables between the groups over time. A greater reduction in the total scores on MOAS in the active tDCS group than the sham tDCS group would be considered a successful primary outcome. Greater reductions in the total scores on BPI and greater increases in Stop Signal Reaction Time in the active tDCS group than the sham tDCS group would be considered successful secondary outcome. A *p* value of < 0.05 will be considered as statistically significant for the primary outcome measure. For secondary outcomes, multiple comparisons will be controlled for with Bonferroni correction and a *p* value of less than 0.0125 will be considered statistically significant.

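### LOCF as the first-line rule scores anyone who stops during treatment and has no later MOAS as exactly unchanged, including those stopped for worsening aggression

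*Protocol article*

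**What the plan says.** The missing-data section of the protocol article ({20c}), whose heading also covers non-adherence, gives the first-line rule: "Data will be analysed on an intention-to-treat basis such that the last observations will be carried forward". The alternative follows: "depending on the pattern of missing data in the last observation, e.g. if missing at random, multiple imputations technique will be used".

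The section on discontinuing allocated interventions ({11b}) lists, among the reasons for stopping an individual, "exacerbation of aggressive behaviours expressed as a report of a serious violent incident and/or an increased incidence of self-harm or self-injurious behaviour", as judged by caregivers.

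On timing, the participant timeline ({13}) says "Three tDCS sessions will be delivered over three successive days (one session daily". The primary outcome section says MOAS will "assess aggressive behaviours at baseline, 1 week (day 10), and 1 month (day 38) following the last tDCS treatment"; no MOAS is planned during treatment.

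The primary comparison ({20a}) is stated as "A 2 × 2 Repeated Measures ANOVA will be performed with group allocation" by time, before against after stimulation. Success is "A greater reduction in the total scores on MOAS in the active tDCS group than the sham tDCS group".

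**The concern.** A participant can be taken off treatment because aggression has worsened, and aggression is what the primary outcome measures. Treatment is over before the first post-baseline MOAS is due. If such a participant contributes no later MOAS, the only value to carry forward is baseline, and the analysis records no change for a person whose recorded reason for stopping was a change for the worse.

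The primary test compares change between arms. If stops for worsening, or the degree of worsening, differ between arms, the carried-forward zeros move the contrast. They also add values with no spread, which makes the estimate look more precise than it is. Because {20c} presents LOCF as the way intention-to-treat is carried out, this is a stated rule for the primary analysis and not a detail left open.

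**Working it through.** The protocol gives no figure for this bias, so there is none to reproduce.

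**1. Inputs from the protocol.** Sessions on three successive days; MOAS at baseline, day 10 and day 38; 30 per arm; overall attrition 20% ({14}), which is 0.20 × 60 = 12 people. Not given: the share stopped for worsening, how much they worsen, and whether MOAS is still collected from them. The first two are assumed below.

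**2. Who is affected.** Someone who stops on days 1–3 and has no later MOAS has only a baseline value. LOCF sets day 10 = day 38 = baseline, so change = 0 at both visits. Someone lost between day 10 and day 38 carries the day-10 score, which need not be zero change. Someone who stops sessions but is rated at both visits is not touched by LOCF.

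**3. Shift in the contrast.** Let p be the share of an arm stopped for worsening with no later MOAS, W their true mean worsening in SDs of change, and m the mean change of the others.

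- True arm mean: (1 − p)m + pW
- LOCF arm mean: (1 − p)m + 0
- LOCF minus truth, active minus sham: −(p_A·W_A − p_S·W_S)

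A negative value favours active, since success is a greater fall. With the same W in both arms the size is (p_A − p_S) × W:

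| Active | Sham | W = 0.5 | W = 1.0 | W = 1.5 | Direction |
|---|---|---|---|---|---|
| 10% | 5% | 0.025 | 0.05 | 0.075 | toward active |
| 15% | 5% | 0.05 | 0.10 | 0.15 | toward active |
| 20% | 0% | 0.10 | 0.20 | 0.30 | toward active |
| 5% | 10% | 0.025 | 0.05 | 0.075 | against active |
| equal | equal | 0 | 0 | 0 | none |

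**4. Simulation.** 30 per arm, 4000 runs, SD of change 1, W = 1, t-test on change (equivalent to the 2 × 2 interaction; BIS-11 covariate left out). In sham, participants not stopped change by −0.3. In active they change by a further −0.3 in the two unequal scenarios and −0.5 in the equal one.

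| Stopped, active / sham | True contrast | LOCF contrast | Rejection, true data | Rejection, LOCF |
|---|---|---|---|---|
| 20% / 5% | −0.04 | −0.19 | 5.3% | 11.9% |
| 5% / 20% | −0.48 | −0.33 | 39.6% | 26.9% |
| 20% / 20% | −0.40 | −0.40 | 25.4% | 38.0% |

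The last row shows the variance effect: same contrast, more rejections. It occurs where there is a real difference. With no difference and 10% stopped in each arm, LOCF rejected in 5.0% of runs, so that scenario shows overstated precision and not extra false positives.

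**5. Dropout unrelated to outcome.** If a share q in each arm is lost before day 10, both arm means are multiplied by (1 − q), and a true effect δ becomes (1 − q)δ. With q = 0.20 this is 0.80δ, a shrinkage of 20%. That is the ceiling, because losses after day 10 carry the day-10 score.

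**6. Would a missing-at-random method alone cure it?** Assume 20% active and 10% sham stopped, W = 1, others changing by −0.3 (active) and 0 (sham).

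- Truth: (0.8 × −0.3 + 0.2 × 1) − (0.9 × 0 + 0.1 × 1) = −0.04 − 0.10 = −0.14
- LOCF: 0.8 × −0.3 − 0 = −0.24
- Missing at random, by arm: −0.3 − 0 = −0.30

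Here the missing-at-random result lies further from the truth than LOCF, because baseline-only participants are in effect given their arm's average improvement.

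**The case against.** A reader might infer that everyone taken off treatment for worsening will be scored as unchanged. The protocol does not support that. Section {11b} stops the intervention and does not say that outcome collection stops; MOAS is rated by care staff; {18b} speaks of complete follow-up; and {20c} commits to intention-to-treat. If staff rate these participants at both visits, the problem does not arise. This stands, and it makes the point conditional.

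A reader might also infer that LOCF tilts the trial toward active tDCS, or that the plan expects active treatment to worsen some people. Neither is supported. The direction depends on which arm has more stops for worsening. Section {11b} is a contingency rule, and the adverse events section ({22}) says that no adverse events are anticipated.

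The affected group may be small: worsening has to lead to stopping within a three-day window, and MOAS must then also be missing. The 20% in {14} is attrition from all causes. The shifts above are in SDs of change, and {14} does not say which SD its 0.3 refers to, so the two should not be compared directly.

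Finally, the exact trigger for multiple imputation may be fixed in an analysis plan that is not shown. That answers part of the complaint about choosing a method from the missing-data pattern. It does not answer the choice of LOCF as first line. Nor does the imputation clause clearly cover the participants at issue: its example is data missing at random, and stops for worsening with only a baseline score are the cases least likely to be judged so.

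**Conclusion.** The concern holds in conditional form. The protocol names LOCF as its first-line rule, and on its own schedule that rule gives a change of exactly zero to anyone who stops on days 1–3 and has no later MOAS. The protocol is silent on whether MOAS continues after sessions stop.

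If it does not, the contrast shifts in favour of the arm with more stops for worsening: 0.05–0.15 SD toward active at 15% against 5%, and 0.025–0.075 SD against active at 5% against 10%, for an assumed worsening of 0.5–1.5 SD. With equal rates and equal worsening there is no bias in the contrast, only an understated variance. With equal non-informative dropout a true effect shrinks by at most 20%. Every stopping rate and degree of worsening here is an assumption. The rule should be corrected, but the documents do not show that the primary result will be biased.

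**What to change.** 1. State that the informant-rated MOAS and BPI-S are collected at day 10 and day 38 for every randomised participant, including those who stop sessions, unless consent to data collection is withdrawn. For these participants this step does most of the work.
2. Delete LOCF. Name in advance one primary method that uses all observed data, either a likelihood-based mixed model or multiple imputation by arm, and do not let the missing-data pattern decide between methods.
3. Because that method assumes missing at random, and step 6 of the working shows that it can hide more worsening than LOCF, add a pre-specified sensitivity analysis that imputes worse scores for participants stopped for worsening who have no later MOAS.

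The cost is a few extra informant forms and a little more analysis work. Nothing here asks for a change to the treatment or to the rules for stopping it.

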### Plans to give access to the full protocol, participant-level data, and statistical code {31c}

The full protocol will be made publicly available on Clinicaltrials.gov. Anonymised participant-level data and statistical code can be provided by the principal investigator upon request.

## Oversight and monitoring

### Composition of the coordinating centre and trial steering committee {5d}

A research management group comprising the trial investigators will be established to manage the overall governance of the project and day-to-day operations. The group will meet monthly to discuss progress and to ensure that the study is conducted in accordance with the requirements of the research ethics approval. While it is acknowledged that a trial steering committee can play an important role in maintaining the quality of study conduct, financial constraints precluded the appointment of such committee. However, this study will be conducted under the auspices of Queen’s University and Providence Care Hospital, where rigorous research governance structures are in operation to ensure the quality of study conduct.

### Composition of the data monitoring committee, its role, and reporting structure {21a}

The research management group will be responsible for data monitoring. While we acknowledged that data monitoring is best conducted by an independent committee, financial constraints precluded the appointment of such committee. However, as mentioned earlier, robust research governance procedures are in operation at Queen’s University and Providence Care Hospital to ensure the quality of study conduct.

### Adverse event reporting and harms {22}

tDCS is considered to be a safe technique, but some small risks are recognised. A review of 567 tDCS sessions and from questionnaire responses from 102 participants [33] reported that the most common side-effect (reported by 70% of participants) is that of a tingling sensation under the electrodes. This is present during and shortly after the period of stimulation and has no adverse effects or risks. Fatigue or tiredness during the stimulation is the next common report (by about 35% of participants), and this may continue for a short period afterwards. This may occur when prolonged and uninteresting tasks are used during the experiment. Headaches after stimulation may occur in less than 10% of the participants. Headaches are usually mild and can be treated with normal over-the-counter painkillers, if required. There is no evidence that tDCS leads to any change in frequency or severity of headaches. Overall, less than 20% of the participants rated the stimulation procedure as mildly unpleasant and 80% reported that it was not unpleasant. In theory, tDCS might induce seizures, but this has never been reported in the scientific literature.

Potential risks will be completely disclosed to the participants as well as what to do should participants experience any side effects. For instance, should the tingling sensation become painful, the treatment will be stopped. The psychological or emotional risk is minimal; this risk will be mitigated with education and assurance from the study team. Additionally, participants will be debriefed at the end of each session and advised to contact the principal investigator if they experienced any adverse effects as a result of participation in the study. If a serious adverse event occurs during the treatment sessions, local staff (clinic, hospital, institutional) will be immediately notified and emergency protocols followed. We are not anticipating any adverse events serious or otherwise. However, should one occur, it will be documented and reported to the Research Ethics Board.

### Frequency and plans for auditing trial conduct {23}

On-site study monitoring will be conducted by designated Providence Care Hospital clinical coordinators who will monitor study safety as serious adverse effects are reported or at least every 6 months.

### Plans for communicating important protocol amendments to relevant parties (e.g. trial participants, ethical committees) {25}

Approval to implement important protocol modifications (e.g. changes to eligibility criteria, outcomes, analyses) will be sought from the Queen’s University Health Sciences Research Ethics Board (HSREB). Upon receiving approval, the changes will be communicated in writing to relevant parties (e.g. investigators, trial participants) and the trial record on ClinicalTrials.gov will be amended accordingly.

### Dissemination plans {31a}

The study trial results will be communicated to healthcare professionals, academics and other relevant groups (e.g., policy makers) via conference presentations and publication in a peer-reviewed journal. The results will be communicated to participants via a poster using a simple language and visual aids. Approval to distribute the poster will be sought at a later stage from the research ethics board.

## Discussion

This will be the first randomised controlled trial in the world to assess the efficacy of anodal versus sham tDCS applied to the left DLPFC to reduce impulsivity and aggression in adults with IDD. The proposed study will help elucidate the role of tDCS in reducing impulsivity and incidents of aggression in this population. Assessing the efficacy of repeated tDCS, for instance, delivered daily over a few weeks, and the parameters required to achieve optimal effects will be important considerations in future studies. The results of this study will prompt further research in the field, paving the way for developing targeted interventions for modulating impulsivity and aggressive behaviours in people with developmental disabilities.

## Trial status

Protocol version 5 dated January 7, 2022

Date recruitment begins: July 01, 2021

Approximate date when recruitment will be completed: June 30, 2023.

## Data Availability

The study investigators will have access to the final trial dataset, and there is no contractual agreements that limit such access for investigators. Authorised individuals from Queen’s University and Providence Care Hospital will also have access to the final trial to ensure that the study is conducted in accordance with the parameters of ethics approval.

## Abbreviations

BIS-11: Barratt Impulsiveness Scale version 11
BPI-S: Behavior Problems Inventory Short Form
DLPFC: Dorsolateral prefrontal cortex
IDD: Intellectual developmental disabilities
iTBS: Intermittent theta burst stimulation
MOAS: Modified Overt Aggression Scale
RRI: Rapid-response impulsivity
SSRT: Stop Signal Reaction Time
SST: Stop Signal Task
tDCS: Transcranial direct current stimulation
